#### Data analysis

All adherence interventions or strategies will be described, based on the type of intervention implemented and the setting. The different evaluations methods will then be described in detail by comparing the type of assessments and outcome measures (adherence to ART and viral load). If appropriate, outcome measures will be reported in terms of changes in the prevalence or reduction in the relative risk. Whenever necessary, we will calculate unadjusted risk ratios (RRs) and 95% confidence intervals (CIs) from data provided and present the outcome indicator results in forest plots. Furthermore, we will perform a sensitivity analysis to measure the robustness of our results to the choice of summary statistic and calculated unadjusted risk differences. We will apply a random- effects model to calculate summary RRs and 95% Cl. To test the robustness of the findings, we will re-run the analysis using a fixed effects model. Data will be coded and analysed used STATA version 15.1.

Details for study criteria are presented in Table 1.

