## Abstract

Multiple factors make adherence to antiretroviral therapy (ART) a complex process. This study aims to describe the barriers and facilitators to adherence for patients receiving first-line and second-line ART, identify different adherence strategies utilized and make recommendations for an improved adherence strategy. This mixed method parallel convergent study will be conducted in seven high volume public health facilities in Gauteng and one in Limpopo province in South Africa. The study consists of four phases; a retrospective secondary data analysis of a large cohort of patients on ART (using TIER.Net, an ART patient and data management system for recording and monitoring patients on ART and tuberculosis (TB)) from seven Johannesburg inner-city public health facilities (Gauteng province); a secondary data analysis of the Intensified Treatment Monitoring Accumulation (ITREMA) trial (a randomized control trial which ran from June 2015 to January 2019) conducted at the Ndlovu Medical Center (Limpopo province); in-depth interviews with people living with Human Immunodeficiency Virus (PLHIV) who are taking ART (in both urban and rural settings); and a systematic review of the impact of treatment adherence interventions for chronic conditions in sub-Saharan Africa. Data will be collected on demographics, socio-economic status, treatment support, retention in care status, disclosure, stigma, clinical markers (CD4 count and viral load (VL)), self-reported adherence information, intrapersonal, and interpersonal factors, community networks, and policy level factors. The systematic review will follow the Preferred Reporting Items for Systematic Reviews and Meta-Analysis (PRISMA) reporting and Population, Interventions, Comparisons and Outcomes (PICO) criteria. Analyses will involve tests of association (Chi-square and t-test), thematic analysis (deductive and inductive approaches) and network meta-analysis. Using an integrated multilevel socio-ecological framework this study will describe the factors associated with adherence for PLHIV who are taking first-line or second-line ART. Implementing evidence-based adherence approaches, when taken up, will improve patient’s overall health outcomes. Our study results will provide guidance regarding context-specific intervention strategies to improve ART adherence.

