### Research questions and hypotheses

What are the demographic characteristics and clinical indicators associated with virological failure and being lost to follow-up (LTFU) in PLHIV taking first-line and second-line ART in urban communities?Hypothesis: Demographic and clinical characteristics are associated with virological failure and being LTFU in patients on ART from complex, and highly mobile urban communities.What are the intra-and inter-personal factors (demographic, socio-economic characteristics), social and community level factors (poverty, social norms, HIV related stigma, culture), structural factors (health systems, support services) and clinical indicators associated with self reported adherence, pill count and virological failure to first-line and second-line ART in rural communities?Hypothesis: Individual and community level factors are associated with self-reported non-adherence, suboptimal pill count, and virological failure in patients on ART in the rural setting.What are the perspectives of virally suppressed and unsuppressed first-line and second-line ART patients about treatment adherence in selected urban and rural communities?
Are there any differences between people receiving first-line and second-line ART?Are there any differences in treatment taking behaviours between virally suppressed and unsuppressed ART patients?What do virally suppressed and unsuppressed ART patients recommend as adherence strategies?Hypothesis: In South African communities, treatment taking behaviour, perceptions of adherence, and recommendations for adherence interventions differ between PLHIV who are virally unsuppressed and those who are virally suppressed.What treatment adherence strategies and interventions have been implemented and evaluated in sub-Saharan Africa for HIV, hypertension, and DM?Hypothesis: There are no differences in the effectiveness of adherence interventions implemented in sub-Saharan Africa for HIV, hypertension, and DM.

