### Materials and methods: Phase IV

Objective 4: Assess and compare adherence intervention strategies for the chronic conditions of HIV, hypertension and DM which have been tested and implemented in sub-Saharan Africa (Title: Adherence strategies and interventions for selected chronic conditions in sub-Saharan Africa: a systematic review and meta-analysis) (see S4 Appendix Systematic review protocol).

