#### Data collection

A pre-defined data sheet will be developed for data extraction. The tool will include (but not be limited to): reference (author, title), year of publication, setting or location, sample size, intervention description, participants receiving adherence (in case of comparison) (see S1 Appendix study codebook). The form/tool will be tested before conducting the final searches. One reviewer will conduct all the data extraction while a second reviewer will be responsible for data quality assurance on the extraction and also conduct full text review of the included material.

We will search using several electronic databases. These will include PubMed/Medline, Web of Science, Google Scholar, Scopus, and CINAHL. If necessary, we will contact study authors and request more information on individual studies. Citations and bibliographies of records will be reviewed to identify additional relevant material.

The basic search terms included will be:

*“Chronic conditions”* OR *“hypertension”* OR *“high blood pressure”* OR *“blood pressure”* OR *“arterial hypertension”* OR *“mellitus diabetes type I”* OR *“mellitus diabetes type II”* OR *“Diabetes”* OR *“Sugar”* OR *“HIV”* OR *“Antiretroviral Therapy”* OR *“Antiretroviral Treatment”* OR *“ART”* OR *“ART Programs”* OR *“ART Programmes”* AND *“adherence”* OR *“compliance”* AND *“interventions”* OR *“strategies”* OR *“odds ratio”* OR *“risk ratio”* OR *“evaluation”* OR *“impact”* OR *“effectiveness”* OR *“outcome”* AND *“sub-Saharan Africa”* OR *“sub Saharan Africa”* OR *“sub-Saharan African”* OR *“sub Saharan African”* OR *“Africa”* (Table 1).

**Table 1 pone.0261107.t001:** Methodological aspect of the systematic review.

Criteria for study inclusion	Components details
Population (P)	Patients with selected chronic conditions (HIV, hypertension, dDM) in sub-Saharan Africa
Intervention (I)	All interventions listed/described as adherence interventions or strategies for the conditions of HIV, hypertension, DM
Comparisons (C)	Standard of care and other adherence interventions reported on in the review
Outcome (O)	The included studies should report any measurement of adherence to chronic conditions—primarily, effects on adherence behaviour and the changes in health outcomes. There is no preferred measurement for reporting; should there be adequate statistical reporting, a meta-analysis will be considered.
Setting	All studies from sub-Saharan Africa only will be considered for the review.

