Language	There will be no language restrictions.
Date	There will be no date/time restrictions.
Publication status	All the documented studies will be considered and included for review. This includes peer reviewed (i.e., papers, manuscripts, and abstracts).
Method	The study will be designed and reported according to PRISMA. PICO will be used as a search strategy approach. This study will describe reported adherence programmes and strategies. There will be a focus on behaviour change techniques used or reported changes in process outcomes of adherence programmes and methods of implementation for HIV, hypertension and /or DM.
Search strategy and selection procedure	We will search using several electronic databases. These will include: PubMed/Medline, Scopus, CINAHL, Web of Science and Google Scholar.
Search terms	(chronic conditions OR hypertension OR high blood pressure OR blood pressure OR arterial hypertension OR mellitus diabetes type I OR mellitus diabetes type II OR Diabetes OR Sugar OR HIV OR Antiretroviral Therapy OR Antiretroviral Treatment OR ART OR ART Programs OR ART Programmes) AND (adherence OR compliance) AND (interventions OR strategies OR odds ratio OR risk ratio or evaluation OR impact OR effectiveness OR outcome) AND (sub-Saharan Africa OR sub Saharan Africa OR sub-Saharan African OR sub Saharan African OR Africa)

The search terms will be adjusted to suit the database being searched. An inventory with the database searched, the corresponding search criteria used, the date when the searches were conducted, and the results will be maintained. A second reviewer will run the searches separately for comparison. The strength of the body of evidence (quality of evidence), the risk of bias and magnitude of effect will be rated and assessed using Grading of Recommendations Assessment, Development and Evaluation (GRADE) [61,62].

*Outcome*. The primary outcome will be adherence to antiretroviral therapy, defined as the proportion of patients meeting the defined adherence criteria. The secondary outcome will be proportion of patients achieving viral suppression, as defined by the study. Outcome (and impact) measures will be reported in terms of changes in the prevalence or reduction in the relative risk. Should there be adequate statistical reporting, a meta-analysis will be considered [63].

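### Phase IV is announced as a network meta-analysis but specified as conventional pooled risk ratios, which as written give no formal comparison between adherence strategies

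*Protocol article*

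**What the plan says.** The abstract of the protocol article names "thematic analysis (deductive and inductive approaches) and network meta-analysis" among the planned analyses. Under Materials and methods: Phase IV, the review carries the title "Adherence strategies and interventions for selected chronic conditions in sub-Saharan Africa: a systematic review and meta-analysis", in which the word network does not appear.

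Objective 4 in the same section is to "Assess and compare adherence intervention strategies for the chronic conditions of HIV, hypertension and DM". The matching hypothesis, under Research questions and hypotheses, reads "There are no differences in the effectiveness of adherence interventions implemented in sub-Saharan Africa for HIV, hypertension, and DM".

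The Phase IV Data analysis section sets out the synthesis. For the effect measure it says "Whenever necessary, we will calculate unadjusted risk ratios (RRs) and 95% confidence intervals (CIs) from data provided". For pooling it says "We will apply a random- effects model to calculate summary RRs". It adds two sensitivity analyses: risk differences in place of risk ratios, and fixed effects in place of random effects. Grouping by type of intervention appears only in the sentence on how the interventions will be described.

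The comparator row of Table 1 admits "Standard of care and other adherence interventions reported on in the review". Table 1 has no row for study design. The Phase IV Sampling/Sample size section refers inclusion to a separate review protocol, which is not shown.

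**The concern.** A network meta-analysis and a conventional pairwise meta-analysis are different models with different estimands. The first estimates every contrast between interventions jointly, including those never tested head to head, and needs defined nodes, a common comparator and a check that direct and indirect evidence agree. The second gives a summary against whatever comparator the pooled studies share. A reader of the abstract expects the first; a reader of the methods finds the second.

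The mismatch matters because the objective and the hypothesis are about differences between interventions. The Phase IV analysis section provides summary RRs but no between-strategy contrast, subgroup test or meta-regression. The mixed comparator row suits a network, where each comparison keeps its place. In a conventional pool it is a hazard unless a rule separates comparisons with standard care from comparisons with another active strategy, and the article gives none.

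A conditional worry follows from the effect measure. Crude RRs recalculated from counts ignore clustering in cluster-randomised studies and leave confounding in non-randomised ones. Phase IV feeds the study's recommendations on adherence strategies, so an uninterpretable or over-precise summary would carry through to them.

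**Working it through.** Phase IV states no sample size, number of studies, event rate or effect size, so there is no figure to reproduce. The first step sets the text side by side. The later steps are illustrations, and **every numerical input in them is an assumption**.

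**1. The stated methods.**

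| Place in the protocol article | Synthesis named |
|---|---|
| Abstract | Network meta-analysis |
| Phase IV, review title | Meta-analysis |
| Phase IV, Data analysis | Random-effects summary RRs; fixed-effects re-run; risk differences as sensitivity analysis |
| Phase IV, Objective 4 | Comparison of strategies |

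The Data analysis section has no nodes, common comparator, consistency check or between-strategy test. It therefore describes a different analysis from the abstract, and one that does not supply the comparison in the objective.

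**2. Mixing comparators.** Assume every strategy has RR 1.20 against standard care, strategies are equal to each other (RR 1.00), and studies have equal weight on the log scale. With a share s of studies using an active comparator, the pooled RR = exp[(1 − s) × ln 1.20 + s × ln 1.00].

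- s = 0: 1.200
- s = 0.25: 1.147
- s = 0.50: 1.095

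The last value describes neither the effect against standard care nor the contrast between strategies.

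**3. Pooling across strategies.** Assume two strategies with RRs of 1.05 and 1.30 against standard care. An equal-weight pool of both gives √(1.05 × 1.30) = 1.168. The contrast that Objective 4 asks for is 1.30 / 1.05 = 1.238, and the pooled value does not show it.

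**4. Clustering, if cluster trials are eligible.** With m patients per cluster, the design effect is DE = 1 + (m − 1) × ICC. The coverage of one study's nominal 95% interval that ignores clustering is 2Φ(1.96/√DE) − 1.

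| m | ICC 0.01: DE, coverage | ICC 0.05: DE, coverage |
|---|---|---|
| 20 | 1.19, 92.8% | 1.95, 84.0% |
| 50 | 1.49, 89.2% | 3.45, 70.9% |
| 100 | 1.99, 83.5% | 5.95, 57.8% |

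**5. Confounding, if non-randomised studies are eligible.** Assume no true effect, and adherence of 85% in good-prognosis and 65% in poor-prognosis patients. The comparison arm has half of each, so its adherence is 0.5 × 0.85 + 0.5 × 0.65 = 0.75.

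- 60% good prognosis in the intervention arm: 0.6 × 0.85 + 0.4 × 0.65 = 0.77; crude RR 0.77/0.75 = 1.027
- 70% good prognosis: 0.7 × 0.85 + 0.3 × 0.65 = 0.79; crude RR 0.79/0.75 = 1.053

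**6. Individually randomised trials.** A simulation with 150 patients per arm and adherence of 65% against 78% gave 95.2% coverage for the unadjusted RR interval. The crude RR is not at fault there.

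**7. The stated sensitivity analyses.** Moving from random to fixed effects, or from RR to risk difference, reuses the same crude counts and the same within-study variances that ignore clustering. Neither switch would reveal the problem in step 4 or in step 5.

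**The case against.** The strongest reply is that much of this depends on a review protocol that is not shown, and that a condensed four-phase article need not repeat it. A good part of that stands, and it rules out three stronger readings that a reader might infer.

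- **That everything goes into a single pool.** The article speaks of summary RRs in the plural, describes interventions by type and setting, and names two outcomes. Separate pools are not excluded. The comparator row of Table 1 is an inclusion criterion, not a pooling rule, so the dilution in step 2 would occur only if the two kinds of comparison were merged. Pooling itself depends on adequate statistical reporting.
- **That any study design may enter.** Table 1 has no design row, but eligibility is referred to the separate review protocol. The sentence "All the documented studies will be considered and included for review" stands in the row on publication status and concerns type of publication.
- **That the interval is bound to be wrong.** Unadjusted RRs are valid for individually randomised trials. The article calculates them only where necessary, which can be read as a fallback, and it plans to rate risk of bias with GRADE. Undercoverage needs uncorrected cluster trials and bias needs crude non-randomised estimates; the documents establish neither. At an ICC of 0.01 with clusters of 20, the loss of coverage is small (92.8%). The figures in step 4 are for one study's interval, not for the pooled one.

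What the reply does not meet is the contradiction. The abstract and the Phase IV analysis section name different syntheses, whatever the review protocol contains. Even if several pools are intended, separate summaries without a stated contrast do not test a hypothesis about differences. GRADE rates certainty; it does not correct an estimate or its interval.

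**Conclusion.** The point holds in a limited form. The article states two incompatible syntheses for Phase IV, and the one it spells out gives no formal contrast between strategies, although the objective and the hypothesis call for one. This rests on the article's own text and needs no assumption.

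The remaining parts are conditional. If a conventional pool did not separate standard-care from active comparators, it would mix two effects, for example giving about 1.10 where the components are 1.20 and 1.00 in equal shares. If cluster-randomised studies enter uncorrected, a single study's nominal 95% interval could cover between about 93% and 58% of the time over the assumed ranges of ICC and cluster size. If non-randomised studies enter crude, moderate imbalance could produce RRs of about 1.03 to 1.05 with no true effect. The documents give none of these inputs, so the figures show what could happen, not what the review will find.

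This should be corrected before the synthesis is run.

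**What to change.** Make the abstract and the Phase IV Data analysis section name the same method. Either of two routes would serve:

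1. A random-effects network meta-analysis by intervention class, with standard of care as the common node and a check of consistency between direct and indirect evidence.
2. Pairwise random-effects pools by intervention class against standard of care only, with a stated test between classes, and the word network deleted from the abstract. Studies comparing two active strategies would be summarised apart.

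Under either route, state what happens if the review protocol admits designs other than individually randomised trials. For cluster trials, use the reported cluster-adjusted estimate or apply a design effect. For non-randomised studies, use adjusted estimates and pool them separately from randomised trials.

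The cost is wording and analysis effort, fewer studies in each pool, and wider intervals. If the review protocol already contains these rules, the change reduces to correcting whichever of the two sections is wrong and adding a sentence that states the between-strategy contrast.

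### Phase IV: unadjusted risk ratios computed from raw counts would ignore clustering in any group-allocated study, and the planned robustness checks would not show it

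*Protocol article*

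**What the plan says.** All of this is in the Protocol article, Materials and methods: Phase IV.

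- **Effect measure (Data analysis).** The sentence opens with a condition, that this is done where necessary, and continues: "we will calculate unadjusted risk ratios (RRs) and 95% confidence intervals (CIs) from data provided and present the outcome indicator results in forest plots".
- **Pooling (Data analysis).** "We will apply a random- effects model to calculate summary RRs and 95% Cl".
- **Robustness checks (Data analysis).** One tests the "robustness of our results to the choice of summary statistic and calculated unadjusted risk differences". The other changes the model: "To test the robustness of the findings, we will re-run the analysis using a fixed effects model".
- **Outcome (Data collection).** The primary outcome is binary, "defined as the proportion of patients meeting the defined adherence criteria". The secondary outcome is the proportion with viral suppression.
- **Eligibility.** Table 1 lists population, intervention, comparison, outcome, setting, language, date and publication status. None of these rows limits study design. The Sampling/Sample size section leaves the inclusion criteria to the registered review protocol (S4 Appendix), which is not shown.
- **Extraction sheet (Data collection).** The named items include "sample size, intervention description, participants receiving adherence (in case of comparison", and the list is expressly open-ended.
- **Whether pooling happens.** Meta-analysis is to be considered if statistical reporting is adequate.

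The article does not mention group allocation, ICCs, design effects or effective sample sizes.

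**The concern.** Adherence strategies can be allocated to whole clinics or communities. The article's Research gap section names adherence clubs and targeted counselling, which lend themselves to delivery by clinic. Patients in one clinic tend to resemble each other, so arm totals from such a study carry less information than the patient count suggests. A risk ratio and interval computed from those totals treat every patient as independent. The point estimate is unchanged, but the interval is too short and the inverse-variance weight too large.

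The rule applies where recomputation is judged necessary, and the article does not say when that is. The likely case is a report with no usable risk ratio, where a clustering adjustment is also most likely to be missing.

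Neither check would expose this. An unadjusted risk difference rests on the same independence assumption. The fixed-effects re-run is where the excess weight is largest, so it could seem to confirm a falsely precise result. The Study design section says that the results of all phases will be brought together into recommendations for adherence strategies in South Africa, so false precision here could carry into them.

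**Working it through.** The plan states no ICC, cluster size or expected number of group-allocated studies, so there is no figure of its own to reproduce. **Every numerical input below is an assumption**, with a range shown.

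**Formulas**

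- Design effect: DE = 1 + (m − 1) × ICC, with m patients per cluster.
- Naive variance of log RR: v = (1 − p1)/(n·p1) + (1 − p0)/(n·p0).
- Correct variance: v × DE, so the correct interval is √DE times as wide on the log scale.
- False-positive rate of one naive study under the null: 2 × [1 − Φ(1.96/√DE)].
- Weight overstatement: (v·DE + τ²)/(v + τ²). Setting τ² = 0 gives fixed effects.

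**One study.** Assume 300 patients per arm in 6 clusters of 50, with 80% against 70% adherent (240 and 210 events).

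- RR = 0.80/0.70 = 1.143, and log RR = 0.1335.
- v = 0.20/240 + 0.30/210 = 0.000833 + 0.001429 = 0.002262. The naive SE is 0.0476 and the naive 95% CI is **1.041 to 1.255**.
- At ICC 0.05, DE = 1 + 49 × 0.05 = 3.45 and √3.45 = 1.86. The correct SE is 0.0476 × 1.857 = 0.0883 and the correct 95% CI is **0.961 to 1.359**.

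In this example the naive interval excludes 1 and the correct one does not.

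**Range over m and ICC**

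| m | ICC | DE | Correct CI wider by | Single-study false-positive rate (nominal 5%) |
|---|---|---|---|---|
| 50 | 0.01 | 1.49 | 1.22 | 11% |
| 30 | 0.05 | 2.45 | 1.57 | 21% |
| 50 | 0.05 | 3.45 | 1.86 | 29% |
| 50 | 0.10 | 5.90 | 2.43 | 42% |
| 100 | 0.05 | 5.95 | 2.44 | 42% |

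Over the wider range of m = 10 to 100 and ICC 0.01 to 0.10, the interval should be 1.04 to 3.30 times as wide. Coverage of the naive 95% interval runs from 94.0% down to 44.7%. At ICC 0 nothing changes.

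**Weight in the pool** (m = 50, ICC 0.05, v as above)

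| τ² | Weight overstated by |
|---|---|
| 0 (fixed effects) | 3.45 |
| 0.005 | 1.76 |
| 0.01 | 1.45 |
| 0.05 | 1.11 |

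**False-positive rate of the pooled result.** Simulation with true RR 1, 70% adherent, 6 clusters of 50 per arm, ICC 0.05, beta-binomial clustering, and inverse-variance fixed-effects and DerSimonian-Laird random-effects pooling (rounded):

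| Pool | Model | Naive | With DE applied |
|---|---|---|---|
| 10 studies, 5 clustered | random effects (primary) | about 7% | about 4% |
| 10 studies, 5 clustered | fixed effects (re-run) | about 18% | about 5% |
| 3 studies, all clustered | random effects (primary) | 12 to 13% | about 3% |
| 3 studies, all clustered | fixed effects (re-run) | 27 to 28% | 4 to 5% |

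Under random effects, the estimated between-study variance absorbs part of the error. Large pooled errors need the fixed-effects re-run or a small pool made up only of group-allocated studies.

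**The case against.** The strongest reply is that the article does not fix as much as it seems to, and that a fuller document governs Phase IV. Several parts of this stand.

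- **Recomputation is conditional.** A reader might infer that every study is recomputed and that published cluster-adjusted intervals are thrown away. The text does not support that. The sentence opens with a condition, and a reported adjusted estimate can be used under it.
- **Design eligibility is not set here.** A reader might take "All the documented studies will be considered and included for review" as admitting any design. That sentence is in the Publication status row of Table 1 and concerns publication type. Eligible designs are left to S4. All that can be said is that the article excludes no group-allocated study.
- **The extraction list is open.** Unit of allocation, number of clusters and ICC are not named, but the list does not rule them out, and study authors may be contacted for more information.
- **S4 may already deal with clustering.** An article need not repeat that, so its silence alone would not be a finding.
- **Pooling is conditional, and the main-model effect in a mixed pool is modest.**

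What the reply does not remove is that the article states a calculation rule of its own: unadjusted, from the data provided, with unadjusted risk differences as a check. Applied to arm totals of a group-allocated study, that rule gives a wrong interval. The forest-plot intervals would be affected even if nothing were pooled.

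**Conclusion.** The point holds in limited form. Wherever risk ratios are computed from raw counts of a group-allocated study, the stated rule ignores clustering. The interval is then too narrow by √DE, which is 1.86 at an assumed 50 per cluster and ICC 0.05, and 1.22 to 2.43 for ICC 0.01 to 0.10 at that cluster size. The weight is overstated by the full design effect in the fixed-effects re-run and by less under random effects. The planned checks cannot detect either error.

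For the primary model in a mixed pool the inflation is small, at about 7% against a nominal 5%. The larger figures belong to single studies, to the fixed-effects re-run or to an all-cluster pool. All sizes rest on assumed ICCs, cluster sizes and adherence rates. The effect is nil if no group-allocated study is included, or if reported cluster-adjusted estimates are used. The documents do not show that the full review plan lacks a clustering rule. They show only that the rule printed in the article needs a qualifier.

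**What to change.** First check S4. If it already covers clustering, a cross-reference in the Phase IV Data analysis section is enough. If not, amend that section as follows:

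1. Group-allocated studies enter with their reported cluster-adjusted estimate and CI.
2. Where none is reported, divide both events and sample size by 1 + (m − 1) × ICC before computing the RR. This leaves the RR unchanged and multiplies its log-scale variance by the design effect. In the example, 300 per arm becomes 300/3.45 = 87, and events become 240/3.45 = 69.6 and 210/3.45 = 60.9.
3. Use the study's own ICC where given, otherwise an assumed 0.05 with sensitivity at 0.01 and 0.10.
4. Apply the same treatment in the RR, risk-difference, random-effects and fixed-effects analyses.
5. Record unit of allocation, number of clusters and ICC on the extraction sheet.

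The cost is a short addition to the analysis text and three extraction fields, with no new data collection. The drawbacks are wider intervals for those studies and reliance on an assumed ICC where none is reported, which is why the ICC sensitivity range is needed.
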